### Sample size {14}

Sample size estimation is based on a Z-test with non-pooled variances to verify the non-inferiority of treatment with LIPUS compared to surgical treatment. A fracture-healing rate of 86% is assumed in the surgical treatment group based on previous studies [6]. In the intervention group, a fracture healing rate of 75% is assumed [6, 9–14]. Since spontaneous healing, i.e. healing without treatment, only occurs in an estimated 5% of cases, it can be assumed that both treatments are superior to no treatment.

LIPUS treatment is assumed non-inferior to surgical treatment if the proportion of fracture healings in the intervention treatment group is less than 25 percentage points lower than in the control group. If a fracture-healing rate of 86% is assumed with surgical treatment and LIPUS treatment is actually non-inferior to surgical treatment, this means that fracture healing can be expected in more than 61% of those treated with LIPUS. In these, surgical intervention can be avoided and all the risks associated with it (e.g., re-hospitalization, secondary diseases or side effects of surgery such as infections and anesthetic incidents). Patients, whose fractures have not healed, will still be able to undergo surgical intervention at a later date. Assuming healing rates of 86% for surgical and 75% for LIPUS treatment, patients with incomplete fracture healing would be considered as treatment failures, included in the 14% or 25% unsuccessful treatment outcomes. Since no relevant side effects are to be expected from LIPUS treatment, the risk of delayed fracture-healing in the event of unsuccessful LIPUS treatment is therefore offset by the risk of unnecessary surgical intervention. The non-inferiority threshold of −25 percentage points is considered appropriate in this context.

With the above assumptions, a one-sided significance level of 2.5% and a power of 90%, 166 patients are required per group. In addition, a dropout rate of 10% is assumed. The proportion of dropouts of max. 10% appears realistic, as patients with non-unions require regular clinical and radiological check-ups (timed to coincide with the study visits) even without participating in the study. The intention-to-treat (ITT) analysis will be used to include patients who will not comply with the protocol. Based on the above assumptions, 184 patients will have to be recruited per treatment group. Accordingly, a total number of 370 cases will be required.

### Recruitment {15}

As part of the study preparations, the study sites were asked in advance to estimate the number of possible patients in order to be able to assess whether a sufficient number of patients could be realized with the 20 study sites. Recruitment will be checked in real time by the central data management of the Center for Clinical Trials Essen (ZKSE). The project management will be in close contact with the sites in order to resolve possible difficulties in recruiting patients at an early stage through regular communication with the study teams. The sites will also be supported centrally and locally by a monitor.

## Assignment of interventions: allocation

### Sequence generation {16a}

Randomization is carried out using the software Clincase developed by Quadratek (Berlin). In order to obtain comparable groups, randomization will be stratified by upper or lower extremity, age (≤ 60 or > 60 years) and sex in order to achieve balanced factor distributions for these relevant predictors. Other variables that could have an important influence on the primary outcome are assumed to be evenly distributed across the treatment arms by randomization. Each randomized patient will be part of the ITT analysis.

### Concealment mechanism {16b}

Considering the given strata information, the study team will perform the randomization by use of the eCRF. The system will provide a randomization code based on a randomization list and will also record the respective result. The system will provide a randomization code based on a randomization list and will also record the respective result. Only authorized people of the ZKSE and the eCRF provider will have access to the randomization list.

### Implementation {16c}

The randomization-ID list will be created by an independent statistician and will be stored in the randomization software. Randomization will be performed dynamically based on the minimization procedure. The information regarding the allocation of patients to the corresponding group will be generated by the software system and automatically communicated to the study site.

## Assignment of interventions: blinding

### Who will be blinded {17a}

PiNGUin is designed as an open-labelled study, as blinding of patients and treating investigators is not possible due to the use of the ultrasound device or the implementation of surgery. A possible bias will be mitigated by the blinded endpoint committee. To assess the primary endpoint, the last available X-ray/CT image of each patient will be presented to the independent endpoint committee. This means that the assessor will not be able to draw any conclusions as to whether, for example, implants have been replaced. As a result, it will be more difficult for the reviewer to assign the patients to the respective arm, which mitigates a possible subjective bias towards one type of treatment.

### Procedure for unblinding if needed {17b}

Not applicable, as the investigators and patients will not be blinded.

## Data collection and management

### Plans for assessment and collection of outcomes {18a}

Data will be derived from paper-based or electronic patient records, depending on the systems used by the respective study site. Data will be collected via the electronic data capture software Clincase (Quadratek Data Solutions Ltd., Berlin). The software has an integrated audit trail and is a GCP-compliant data management system. All data management will be carried out in accordance with harmonized standard operating procedures (SOPs). As part of the data collection at the centers, the ZKSE will provide predefined communication channels to give the centers the opportunity to raise questions or concerns. Source data will be reviewed by the monitor during on-site visits.

### Plans to promote participant retention and complete follow-up {18b}

If a patient does not appear to a planned study visit, the respective study personnel will attempt to contact the patient and reschedule the missed visit as soon as possible. The patient will be informed about the importance of keeping the assigned appointment and it will be ensured whether the patient wants and/or should continue in the study. Before a patient will be classified as “lost to follow-up”, the investigator or a member of the study team must make every effort to re-establish contact with the participant (three phone calls if possible and, if necessary, writing to the participant's last known mailing address). These attempts at contact will be documented in the participant's medical record. Data collected for the patients up to the time of withdrawal from the study will be used for analysis.

### Data management {19}

The ZKSE will take technical and organizational measures that meet the requirements of the relevant data protection regulations in order to adequately protect the data from misuse and loss. All electronic data will be stored on physical or virtual servers at Essen University Hospital. Study data of the study sites will be collected via the web-based electronic data collection system (EDS) software Clincase. The primary storage of these data will take place on servers in two Quadratek data centers in Berlin. After the database will be closed, the data will be finally exported and transferred to the servers of the University Hospital Essen and the data in the Quadratek data centers will then be deleted. Storage of data on local PCs of the ZKSE is not permitted. The computers used for the project are protected against external access by a firewall configured by the hospital computer center of Essen University Hospital. User management is implemented under Windows. Remote access to the data is excluded. Only the people involved in the project will have access to the data. The ZKSE, as an independent institution from the other study personnel, will be responsible for data quality management and monitoring of this study. Data will be checked for missing data, data out of range, inconsistent or potentially incorrect by date management. For this purpose, checks such as ranges, date inconsistency or presence/absence of data or complex cross-form checks such as date discrepancies between visits will be carried out. Specific accuracy and reliability checks will be performed automatically while the forms in the software are completed to enable immediate quality control. Data management will perform further manual checks for completeness and plausibility of the study data and will clarify any question with the study centers electronically via the software. Further checks for plausibility, consistency and completeness of the data will be carried out after completion of the study. An audit trail will ensure the traceability of all changes made in the database. If no further corrections are to be made, the database will be closed and the final export will be used for the statistical analysis. The pseudonymized clinical data will be managed and analyzed at the University Hospital Essen, Institute for Medical Informatics, Biometry and Epidemiology/Center for Clinical Trials Essen as part of data management and statistical evaluation. Only the project staff will have access to the project-specific data in accordance with the rights assigned to them personally. All data manipulations will be documented in log files, which will contain the type of manipulation, the time and the user ID. These log files will be protected against unauthorized access and will only be accessible to administrators in an emergency.

### Confidentiality {27}

The study will be conducted in accordance with the GCP guidelines and the Declaration of Helsinki. Data protection will be ensured in all phases of data collection, transmission, processing and analysis in accordance with the laws and regulations of the Federal Republic of Germany and international standards. The integrity, confidentiality and availability of personal data will be ensured in accordance with the General Data Protection Regulation (GDPR). The principle of purpose limitation of data collection, transmission and evaluation will be observed and the confidentiality of the data will be guaranteed both for the employees and for the subcontractors/data processors. Confidentiality of study patients will be ensured by pseudonymization of patient data in the EDC system. The data collected will be deleted no later than 10 years after the end of the clinical study ((EU) 2017/745, Annex XV, Chapter III, Sect. 3).

### Plans for collection, laboratory evaluation and storage of biological specimens for genetic or molecular analysis in this trial/future use {33}

Not applicable as no laboratory evaluation or storage of biological specimens will be carried out in this study.

## Statistical methods

### Statistical methods for primary and secondary outcomes {20a}

Treatment with LIPUS will be analyzed with a non-inferiority test against surgical treatment for the primary endpoint of fracture healing. A one-sided 97.5% confidence interval will be estimated for the difference in the proportion of fracture healing between the two groups. If the lower limit of the confidence interval will be greater than the non-inferiority limit of −25 percentage points, the null hypothesis of no non-inferiority will be rejected at the significance level α = 0.025. In addition, a generalized linear mixed model (GLMM) will be fitted to evaluate the robustness of the result for the binary endpoint of fracture healing. Treatment, sex, age and upper vs. lower limb will be considered as fixed effects. The study sites will be modeled as random effects. In order to estimate the risk difference for the treatment in the GLMM, the identity link will be considered as a link function for this endpoint. In addition, the analyses will be performed separately for radiographic bony consolidation and functional restoration. An intention-to-treat (ITT) analysis will be performed as well as a per-protocol (PP) analysis as a sensitivity analysis. The safety analysis will be based on the documented (S)AEs/(S)ADEs. All secondary endpoints will be analyzed exploratively, that is, without adjustment for multiple testing, using standard methods of statistical inference appropriate for the scale level of the endpoint in question. Scores for DASH and LEFS will be considered as continuous outcomes for which linear mixed regression models will be used, where sex, age, and upper or lower extremity will be included as fixed and study sites as random effects.

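### The primary risk difference is not adjusted for the factors used in allocation, and the one adjusted check names an identity-link mixed model that may not fit near 86% healing

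*Protocol article*

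**What the plan says.** **Allocation.** The section on sequence generation {16a} lists extremity, age (up to 60 or over 60 years) and sex as the factors to be balanced, "in order to achieve balanced factor distributions for these relevant predictors". The section on implementation {16c} adds: "Randomization will be performed dynamically based on the minimization procedure".

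**Primary test.** The section on statistical methods {20a} states: "A one-sided 97.5% confidence interval will be estimated for the difference in the proportion of fracture healing between the two groups". The lower limit is compared with −25 percentage points at α = 0.025. No covariate or stratum is named. The sample size section {14} rests on the same kind of comparison, a Z-test with unpooled variances.

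**Adjusted check.** Section {20a} adds a generalised linear mixed model as a robustness analysis, with treatment, sex, age and limb as fixed effects and site as a random effect. To obtain a risk difference, "the identity link will be considered as a link function for this endpoint". No other link is named. The same section adjusts the secondary DASH and LEFS models for sex, age, limb and site.

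**The concern.** Balancing a prognostic factor at allocation removes its contribution to the between-arm difference, but the crude standard error still counts that variation as noise. The interval is then wider than it need be. The protocol itself calls the three factors relevant predictors and adjusts its exploratory scores for them, yet leaves the confirmatory comparison crude.

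The one model that would show whether adjustment matters is numerically fragile. With an identity link the linear predictor is the probability itself, and a normally distributed site effect on that scale is unbounded. The assumed surgical rate is 86%, so only 14 points lie between the mean and the bound of 1. Section {20a} also repeats the analyses for bony consolidation and functional recovery separately. The composite requires both, so each component rate is at least as high as the composite rate. If the mixed model is repeated for them, it moves nearer the bound.

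At stake are a little precision and the availability of the robustness check. The validity of the primary conclusion is not at stake.

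**Working it through.** **1. Inputs, all from section {14}.** "A fracture-healing rate of 86% is assumed in the surgical treatment group based on previous studies"; "In the intervention group, a fracture healing rate of 75% is assumed"; margin 25 points; one-sided α 2.5%; power 90%.

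**2. The plan's own figure.** The summed variance is 0.86×0.14 + 0.75×0.25 = 0.3079. The distance from the expected difference (−11 points) to the margin is 0.14. So n = 0.3079 × (1.960 + 1.2816)² / 0.14² = 165.06, rounded up to 166 per group. This agrees with "With the above assumptions, a one-sided significance level of 2.5% and a power of 90%, 166 patients are required per group". With 166 per group, SE = √(0.3079/166) = 0.0431 and power = Φ(0.14/0.0431 − 1.96) = 90.2%.

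**3. Cost of leaving the factors out.** Let R² be the share of outcome variance explained by the three factors. This is an assumption, taken from 0 to 10%. If allocation balances them fully, the true SE of the difference is 0.0431 × √(1−R²), while the crude test still uses 0.0431.
- True α of the crude test: 1 − Φ(1.96/√(1−R²))
- Power of the adjusted test: Φ(0.14/(0.0431√(1−R²)) − 1.96)
- Actual power of the crude test: Φ((0.14 − 1.96×0.0431)/(0.0431√(1−R²)))

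| R² | true α, crude | power, adjusted | actual power, crude |
|---|---|---|---|
| 0% | 2.50% | 90.2% | 90.2% |
| 1% | 2.44% | 90.4% | 90.3% |
| 3% | 2.33% | 91.0% | 90.5% |
| 5% | 2.22% | 91.5% | 90.7% |
| 10% | 1.94% | 92.9% | 91.3% |

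Against the planned 90.2%, adjustment adds 0 to 2.7 points. Like for like at R² = 10% it adds 92.9 − 91.3 = 1.6 points, because balance also helps the crude estimate.

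A simulation of 332 patients, balanced within the eight strata, with 4,000 runs per setting, agrees. Power was 90.1–91.9% crude and 90.1–92.9% adjusted. Rejection at the margin was 2.1–3.2% crude and 2.2–3.2% adjusted, so there is no visible difference between the two methods.

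**4. Fragility of the identity link.** A fixed-effects identity-link binomial model (site effect not fitted) was simulated with an assumed mix of 65% lower limb, 30% over 60 and 50% of each sex. The share of runs that did not converge, or that gave fitted values outside 0–1, was:
- no covariate effects: 1–3%
- 5 points for limb and for age: 3–6%
- 10/10/5 points for limb/age/sex: about 32%
- 15/15/5 points: about 70%, a setting in which true probabilities themselves reach 1

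A smaller rerun (400 runs per setting) gave 3%, 2%, 32% and 56%. The pattern holds, but the figure for the extreme setting is loose.

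For the site effect, with a normal site intercept of standard deviation σ and a mean of 86%, the chance that one site exceeds 1 is 1 − Φ(0.14/σ). For at least one of 20 hospitals:
- σ = 0.05: 0.26% per site, 5% overall
- σ = 0.08: 4.0% per site, 56% overall
- σ = 0.10: 8.1% per site, 81% overall

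**5. Sidedness.** The critical value is 1.960 for a one-sided 97.5% and for a two-sided 95% interval. At an observed −11 points the lower limit is −11 − 1.96×4.31 = −19.4 points either way. The two-sided form only adds the upper limit, −2.6 points.

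Non-inferiority is declared when the observed difference is above −25 + 8.4 = −16.6 points. A significantly lower rate is seen when it is below −8.4 points. Under 75% against 86%, the chance of the second is Φ((0.11 − 0.0844)/0.0431) = 72%. The chance of both is 0.724 − Φ((0.11 − 0.1656)/0.0431) = 0.724 − 0.098 = 0.625, or about 63%.

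**The case against.** The crude interval is coherent with the sample size calculation, which reproduces, and any error from omitting the factors runs against a false claim of non-inferiority. A reader might infer that the primary test is invalid or the trial underpowered. The documents do not support that. Power is at least the planned 90%, and the loss is small even at R² = 10%. This stands in full.

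The factors are not absent from the plan: they are in the mixed model and in the subgroup analyses {20b}. That also stands, but neither is the confirmatory estimate.

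A reader might infer that the mixed model will often fail. That is not shown. The failure rates depend wholly on covariate effects and a site variance that the protocol does not give, and the simulations did not fit the planned model with its site effect. The wording on the link is soft, and section {20c} leaves further detail to a statistical analysis plan that is not shown. A missing convergence fallback is therefore no finding. What remains is that the only link the protocol names is a poor default for rates this close to 1.

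A reader might also infer that a one-sided interval is a flaw or hides a lower healing rate. It is not a flaw: the decision is identical under either form. The 63% follows from the assumed rates and the 25-point margin, not from sidedness, and the background section openly states that a lower rate is expected with LIPUS.

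**Conclusion.** The point holds as an inexpensive improvement, not as an error in the test. The confirmatory interval does not use the three factors on which patients are allocated. It is valid and at worst slightly conservative: true α about 1.9–2.5% and about 0–3 points of power against the planned 90.2%, if the factors explain 0–10% of outcome variance. These figures assume that allocation balances the factors fully. Minimisation may balance them less completely within combinations of factors, so the conservatism is an upper estimate.

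The identity-link mixed model is a weak choice for the only adjusted check of the primary endpoint. The chance of a failed or inadmissible fit runs from about 1% to about 70% over the assumed effect sizes. It is low if covariate and site effects are small. The one-sided interval is correct as it stands.

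**What to change.** - Make the primary estimate the risk difference adjusted for extremity, age group and sex, either standardised from a logistic model with treatment and these factors or as a Mantel-Haenszel stratified difference. Compare its lower one-sided 97.5% limit with −25 points, as now.
- Keep the crude difference as a sensitivity analysis.
- Replace the identity-link mixed model with a logistic mixed model with random site, standardised to a risk difference. This still yields a risk difference, and fitted probabilities stay between 0 and 1.
- Optional: report the two-sided 95% interval as well. The decision is unchanged, and readers could see whether a non-inferior result also shows a significantly lower healing rate.

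The cost is wording in the protocol or analysis plan, settled before the data are analysed. The margin, α, sample size and data collection stay as they are.

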### Participant timeline {13} (Fig. 1)

Seven visits will take place at the respective study center. During the screening visit, the inclusion and exclusion criteria are checked, and the patient is informed about the study. If these criteria are met, consent is obtained and the patient is randomized into one of the two groups. Patients receiving LIPUS treatment are prescribed an ultrasound device. For patients in the surgical group, preparations for the operation are made (e.g. anesthesia information). After the patient has been randomized, 7–21 days may elapse before the ordered ultrasound device arrives at the study site, or before all preparations for surgery have been completed and a date has been set. If more than four weeks elapse between randomization and the start of ultrasound therapy or surgery, the inclusion and exclusion criteria must be checked again at the baseline visit for possible changes. Repeated imaging is at the discretion of the attending physician and is performed independently of the study.

At the baseline visit (day 0), patients in the intervention group will receive the ultrasound device and will be instructed on the use. In addition, the site of the non-union to be treated by ultrasound will be marked. Before the start of LIPUS treatment or surgery, baseline data will be collected (Fig. 2) and a physical examination will be performed. In both treatment groups, NRS will be used to evaluate the patients’ pain, and questionnaires will be used to assess the general quality of life (SF-12) and the function of the affected limb (DASH or LEFS).

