### Methods in analysis to handle protocol non-adherence and any statistical methods to handle missing data {20c}

At visit three, approximately 120 days after start of the intervention, it will be established whether the treatment has been successful. If the treatment is classified as unsuccessful for patients, the corresponding patients from both treatment groups will be offered alternative or further treatments, including (renewed) surgery. Should such additional interventions occur after visit 3, the data from visits 4 and 5 should only be viewed with caution. If analyzed according to the ITT principle, positive treatment effects of the surgical intervention could overestimate the effect of the LIPUS treatment. If patients with additional surgical intervention are counted as surgically treated, the effect of LIPUS treatment could also be overestimated, as the patients who failed and therefore underwent surgery are no longer considered in this group. If all patients with an additional procedure were excluded from the analysis, the treatment effects in both groups could be overestimated, as these patients with a failure are no longer included. For the analysis of the primary endpoint, all patients who will receive an additional surgical intervention are therefore classified as failures, as it can be assumed that the intervention was performed due to a lack of success. For the evaluation of the secondary endpoints, the last observed values before an additional surgical intervention will be carried forward (last observation carried forward (LOCF)). Because of the different interventions (non-recurring surgery vs. daily treatment with LIPUS), a smaller compliance rate in the LIPUS group will be expected, resulting in presumably lower success rates. To account for these compliance differences in the application of the treatments, the ITT population will be regarded for primary analyses. In order to estimate the differences of the treatments when applied correctly, the PP population will be analyzed additionally.

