## Discussion

The aim of this G-BA-funded study is to prove that in patients with non-unions, treatment with low-intensity pulsed ultrasound is not inferior to surgical intervention in terms of the fracture healing rate endpoint (non-inferiority question). Despite medical advances, non-unions occur in approximately 2–10% of all fractures and can affect up to 30% if certain risk factors are involved [1, 2]. To date, surgical revision has been the gold standard in the treatment non-union, with the surgical procedure depending on the type of non-union. The disadvantages of surgical intervention are re-hospitalizations associated with the operation as well as possible secondary diseases and side effects such as postoperative infections, anesthetic incidents and embolisms. A possible alternative to surgical revision for non-unions is treatment with LIPUS, although this is currently considered an individual health service and the benefits over surgery have not yet been shown in a comparative study with sufficient certainty of results.

One of the strengths of our study lies in its design. The study will be conducted as an open, controlled and randomized study with 370 patients over 2 years at approximately 20 study sites. Blinding of patients and investigators is not possible due to the nature of the intervention. A possible bias will be significantly attenuated by the choice of an endpoint committee. To assess the primary endpoint (assessment of fracture healing), only the last available X-ray/CT image of the individual patients will be presented to the independent endpoint committee. This means that the assessor will not be able to draw any conclusions as to whether, for example, implants have been replaced, i.e. whether a surgery has taken place.

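### Non-inferiority is claimed from ITT alone, for a reason that considers only LIPUS non-compliance; surgery-arm patients followed up without an operation would favour the claim unchecked

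*Protocol article*

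**What the plan says.** The section on statistical methods {20a} rejects the null hypothesis when the lower limit of a one-sided 97.5% interval for the difference in healing lies above -25 percentage points. On populations it adds: "An intention-to-treat (ITT) analysis will be performed as well as a per-protocol (PP) analysis as a sensitivity analysis".

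The section on non-adherence and missing data {20c} gives the reason. It expects "a smaller compliance rate in the LIPUS group will be expected, resulting in presumably lower success rates", and continues: "To account for these compliance differences in the application of the treatments, the ITT population will be regarded for primary analyses". PP has a descriptive role: "In order to estimate the differences of the treatments when applied correctly, the PP population will be analyzed additionally". No sentence requires PP to agree before non-inferiority is claimed.

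The same section deals with rescue surgery. For the primary endpoint, "all patients who will receive an additional surgical intervention are therefore classified as failures". This applies to both arms.

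Under sequence generation {16a}, "Each randomized patient will be part of the ITT analysis". The article does not say how a patient randomised to surgery but never operated on enters the primary analysis.

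**The concern.** In a non-inferiority trial the two directions of non-adherence are not equivalent. Poor LIPUS adherence lowers the LIPUS rate and makes the claim harder to reach, so ITT is conservative there. That is the only direction the article discusses. Patients in the surgery arm who do not have the operation lower the control rate, shrink the observed deficit and make the claim easier.

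The rule on additional surgery closes the rescue route, because a LIPUS patient who is later operated on cannot count as a LIPUS success. It does not reach the unoperated control patient. Counting that patient as a failure too would deepen the dilution.

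As written, non-inferiority would be declared from ITT even if the planned PP analysis did not exclude a 25-point deficit. The Introduction and Discussion link the conclusion to health-insurance coverage of LIPUS.

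**Working it through.** **Inputs from Sample size {14}:** healing 86% (surgery) and 75% (LIPUS), margin 25 points, one-sided 2.5%, power 90%, unpooled Z-test, 166 per group (184 after 10% dropout), healing without treatment 5%.

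**Assumptions:** the shares of unoperated surgery patients and of non-adherent LIPUS patients are not in the documents and are varied below. Non-adherers heal at 5% (the plan's figure for no treatment) or, in the surgery arm, at 61% (the LIPUS rate at the margin, 86 - 25).

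**The plan's own figure.** n = (1.960 + 1.282)² × (0.86×0.14 + 0.75×0.25) / (0.25 - 0.11)² = 165.1, rounded up to 166. It reproduces.

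**Surgery-arm non-adherence only.** Let q be the unoperated share and h their healing rate. At the margin:

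- control rate p_C = (1 - q)×0.86 + q×h; LIPUS rate p_L = 0.61
- SE = √[p_C(1 - p_C)/166 + p_L(1 - p_L)/166]
- false non-inferiority rate = Φ[(0.25 + p_L - p_C)/SE - 1.96]

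Example, q = 5%, h = 5%: p_C = 0.95×0.86 + 0.05×0.05 = 0.8195; difference -0.2095; SE = 0.0482; Φ(0.0405/0.0482 - 1.96) = Φ(-1.12) = 0.131.

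| Unoperated share | Difference, h = 5% | False rate | Difference, h = 61% | False rate |
|---|---|---|---|---|
| 0% | -25.0 | 2.5% | -25.0 | 2.5% |
| 2% | -23.4 | 5.3% | -24.5 | 3.2% |
| 5% | -21.0 | 13.1% | -23.8 | 4.5% |
| 10% | -16.9 | 37.1% | -22.5 | 7.6% |

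**Non-adherence in both arms**, all non-adherers healing at 5%. The LIPUS rate becomes (1 - r)×0.61 + r×0.05 for a non-adherent share r.

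| LIPUS share | Surgery share | Difference | False rate |
|---|---|---|---|
| 5% | 5% | -23.75 | 4.4% |
| 10% | 10% | -22.5 | 7.2% |
| 5% | 2% | -26.2 | 1.4% |
| 10% | 5% | -26.6 | 1.1% |
| 15% | 10% | -25.3 | 2.2% |

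Equal non-adherence still inflates the error, because each non-adherent surgery patient loses 81 points of healing probability (86 - 5) and each LIPUS patient only 56 (61 - 5). A clear excess on the LIPUS side reverses the sign.

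**Requiring both analyses.** In a simulation with 184 per arm, surgery non-adherers healing at 5% and removed from PP at random, the joint rule holds the false rate at about 2.4% for 5%, 10% or 15% non-adherence. At 86% v 75%, power for PP is 92.8% with 184 per group, 90.2% with 166 and 87.1% with 150. Simulated joint power with 184 randomised per arm is about 92% with 5% non-adherence in the surgery arm only, and about 89% with 5% in both arms.

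**The case against.** The strongest reply is that the article itself expects non-adherence to be greater under LIPUS. If those patients also heal at 5%, the error stays below nominal in the unequal scenarios above. PP is pre-specified, so a discrepancy would be visible. PP alone would not be safer: dropping non-compliant LIPUS patients can raise the LIPUS rate, and the comparison is no longer randomised. All of this stands. It bounds the size and rules out replacing ITT by PP. It does not make PP binding, and it leaves the surgery arm without a stated safeguard.

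Unoperated patients may also leave without an outcome. They would then be missing, handled by complete-data analysis or multiple imputation as the section on missing data provides, which softens the effect. The calculation concerns those who are followed up.

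Some stronger readings are tempting but unsupported:

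- A reader might take 37% as the expected error. It is a worst case: 10% unoperated, 5% healing and no LIPUS non-adherence, with no such share in the documents.
- A reader might think the failure rule covers only LIPUS patients who go on to surgery. It covers additional surgery in either arm.
- The delay after randomisation might be read as evidence that control patients will not be operated on. The participant timeline describes a wait in both arms ("7–21 days may elapse before the ordered ultrasound device arrives at the study site", or until surgical preparations are complete).
- The Discussion's remark on LIPUS that "this is currently considered an individual health service" might suggest that control patients will obtain it elsewhere. It does not say so, and the section on concomitant care does not permit other bone-stimulating therapies. That route would in any case correspond to healing nearer 61% than 5%.

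**Conclusion.** The point holds in a limited form. The article fixes a decision rule based on ITT alone, with a compliance argument that covers only the conservative direction. Surgery-arm patients who are followed up without an operation would move the result towards the claim, and nothing in the decision rule guards against this.

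The size cannot be stated as one number. For 2% to 10% unoperated with full LIPUS adherence, the false rate runs from about 3% to 8% (healing at 61%) or from about 5% to 37% (healing at 5%). Equal non-adherence of 5% or 10% gives 4.4% or 7.2%, and clearly greater LIPUS non-adherence with equally poor healing can take it below 2.5%. These figures assume true rates exactly at the margin, 166 analysed per group, and outcomes observed for non-adherers. They define a false claim by the effect of the treatments as received. This is a worthwhile, inexpensive improvement and does not show that the planned analysis is invalid.

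**What to change.** State that non-inferiority is claimed only if the lower confidence limit exceeds -25 percentage points in both the ITT and the PP analysis. Keep patients with additional surgery in the PP set as failures, so that PP does not discard LIPUS failures. Extend the reasoning in the non-adherence section to surgery-arm patients who are not operated on, and say how they enter the ITT analysis.

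The PP analysis is already planned, so the change needs wording, including a PP definition that carries the failure rule, and no new data. The price is slightly lower power: about 90% for PP with 166 per group and 87% with 150, and jointly somewhat less. No larger sample is needed while PP keeps about 90% of each arm. PP remains a non-randomised comparison, and its error control in the simulation assumes that non-adherence is unrelated to prognosis. It should therefore supplement ITT and not replace it.
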